## Abstract

**Background:**

Patients with chronic kidney disease (CKD) are at increased risk for multiple adverse events, several of which have been proven to be less likely with the use of sodium-glucose cotransporter-2 inhibitors (SGLT2i). As a result, guidelines now recommend SGLT2i be given to those with mild to moderate CKD and type 2 diabetes. The objective of this study is to evaluate if a pharmacist-driven SGLT2i prescribing initiative among eligible patients with CKD and diabetes within the VA could more rapidly improve the adoption of SGLT2i via a pragmatic approach aligned with learning health systems.

**Methods:**

Eligible patients will be identified through an established VA diabetes dashboard. Veterans with an odd social security number (SSN), which is effectively a random number, will be the intervention group. Those with even SSNs will serve as the control while awaiting a second iteration of the same interventional program. The intervention will be implemented in a rolling fashion across one Veterans Integrated Service Network. Our primary outcome is initiation of an SGLT2i. Secondary outcomes will include medication adherence and safety-related outcomes.

**Discussion:**

This project tests the impact of a pharmacist-driven medication outreach initiative as a strategy to accelerate initiation of SGLT2i. The results of this work will not only illustrate the effectiveness of this strategy for SGLT2is but may also have implications for increasing other guideline-concordant care. Furthermore, the utilization of SSNs to select Veterans for the first wave of this program has created a pseudo-randomized interventional trial supporting a pragmatic learning health system approach.

**Trial registration:**

ISRCTN12374636.

**Supplementary Information:**

The online version contains supplementary material available at 10.1186/s12882-023-03446-1.

## Background

Chronic kidney disease (CKD) is a common condition affecting more than 1 in 7, or approximately 15%, of U.S. adults [1]. Through various mechanisms, patients with kidney disease are known to be at heightened risk for cardiovascular disease and cardiovascular events [2, 3]. However, several recent studies have been published documenting the benefit of sodium-glucose co-transporter 2 inhibitors (SGLT2i) on reducing cardiovascular death and major adverse cardiovascular outcomes in patients with CKD, as well as decreasing the development or worsening of nephropathy [4–11]. SGLT2i are a class of drugs approved for the treatment of type 2 diabetes. Given the emerging research that has been produced on the benefits of SGLT2i, the American Diabetes Association (ADA) and the Kidney Disease Improving Global Outcomes (KDIGO) guidelines now recommend that SGLT2i be given to all patients with mild to moderate CKD and type 2 diabetes regardless of their glycemic control [12, 13]. Nevertheless, prescribing SGLT2i for eligible patients remains suboptimal [14–16]. Previous research has indicated that it can take as much as 17 years for evidence to become solidified into routine practice and care [17]. Therefore, given the newfound benefits of SGLT2i in patients with CKD and type 2 diabetes and recent changes to treatment guidelines, what remains unknown is how to effectively implement these guidelines into practice to improve the health of patients with CKD.

Pharmacists play a key role in patient care teams. Numerous studies have demonstrated that integrating pharmacists into the care team results in improved clinical outcomes, decreased health care costs, improved patient experience, and improved care team experience – all aspects of the quintessential Quadruple Aim [18–23]. In addition, pharmacists can prescribe medications in many states, improving their ability to optimize and manage medications. Given their expertise in medication management and the success of other pharmacist-focused interventions, [24–26] an implementation strategy for increasing SGLT2i that incorporates clinical pharmacists holds great promise.

Testing and evaluating implementation strategies, such as pharmacist-driven SGLT2i proactive outreach, also supports and aligns with the principles of learning health systems. A learning health system is one in which internal data and experience are integrated with external evidence to produce knowledge that can be used to improve practice [27]. While the effectiveness of SGLT2i have been well documented, strategies to improve prescribing of this class of medication to eligible patients are needed. In alignment with learning health systems, it is also important that the evaluation of these strategies remain pragmatic in nature so that they can be easily tested, yet maintain scientific rigor to adequately determine effectiveness.

### Aims

Improve the proportion of eligible Veterans with CKD initiated on an SGLT2i through a targeted pharmacy intervention across a series of Veterans Affairs (VA) clinics. In addition, this project aims to inform learning health systems by testing a pragmatic strategy to reach eligible patients.

We hypothesize that patients who receive a targeted pharmacy intervention during the first iteration will have a higher proportion of SGLT2i initiation than those receiving usual care while they await a future wave of this same interventional program.

## Methods

### Study design and setting

The VA is divided into different regional systems of care across the U.S. called Veterans Integrated Service Networks (VISNs). This multicenter interventional study focused on the Midwest VISN, which includes 8 VA health systems across Minnesota, Iowa, North Dakota, South Dakota, and Nebraska. Eligible Veterans are assigned to either a targeted pharmacy intervention or usual care. The study began in February 2022 and will continue until all eligible Veterans in the region are offered the intervention, which is anticipated to be in 2025.

### Ethical and regulatory approval

The Minneapolis VA Health Care System Human Research Protection Program determined that, as a quality improvement initiative, this study did not meet the definition of research and, therefore, did not need institutional review board (IRB) oversight. This determination extends to all VA sites as they are all within the same health system.

### Eligibility criteria

Patients are included in the study if they have the following inclusion criteria:

CKD (defined as estimated glomerular filtration rate (eGFR), as extracted from the VA electronic health record, ≥ 25 mL/min/1.73 m^2^ and eGFR < 60 mL/min/1.73 m^2^ upon two measurements).Type 2 diabetes (defined as either ICD9/10 code of type 2 diabetes or most recent hemoglobin A1c > = 7%).

Patients are excluded if they:

Have type 1 diabetes.Are already prescribed an SGLT2i or GLP-1 medication at the time of data acquisition, which serves as the index date.Have an SGLT2i allergy.Are on dialysis.Have a diagnosis of pancreatic cancer or pancreatitis.

### Patient selection and randomization

As part of their Academic Detailing Diabetes Campaign and to monitor SGLT2i initiation, the VA developed a diabetes dashboard to identify patients who would benefit from an SGLT2i. The dashboard includes the above inclusion criteria and several other demographic and clinical variables. The dashboard is updated daily to reflect eligible patients. One included variable in the dashboard is patients’ social security number. Due to the finite availability of resources, we have utilized a pseudo-randomization of eligible Veterans to determine which Veterans within the VISN receive the intervention first, providing a natural comparison group in those Veterans who will be intervened upon later. For this study, patients with an odd social security number are put in the intervention arm, while those with an even social security number serve as the control. Patient lists will be extracted from the VA dashboard at fixed time points throughout the study and will be considered the dates of randomization. The controls will receive usual care until all eligible Veterans in the odd-numbered group have received the intervention. At that time, even-numbered Veterans will also begin to receive the intervention.

The intervention will be implemented in a rolling fashion, beginning with patients at the Minneapolis VA health system, and other clinics will be subsequently added as outreach is being completed.

### Intervention

The intervention steps are illustrated in Fig. 1. Because the patient lists are pulled at fixed time points, which serve as an index date, a patient may have been prescribed an SGLT2i between when the list is generated and when intervention outreach occurs. For that reason, the first step of the process is that a study team member reviews the patient’s medical record to ensure that they have not already been prescribed the medication and that they meet all other inclusion criteria. However, if a patient is prescribed a GLP-1 between their index date and their date of pharmacist review, they are not subsequently excluded. If patients otherwise continue to meet the study criteria, they are mailed a letter describing the benefits of SGLT2i, informed of the initiative, and instructed that they will receive a call to set up an appointment with the clinical pharmacist. After patients have received their letter, a member of the study team calls them to request their participation and to schedule a visit with the clinical pharmacist. Patients who agree are seen by one of two clinical pharmacists dedicated to this project. Pharmacist appointments are scheduled for 30 minutes, during which the pharmacist assesses the patient’s current medications and disease states that may be impacted by an SGLT2i, such as self-monitored blood glucose levels, perceived life expectancy, and any other relevant information. During this time, the pharmacist also addresses any questions or concerns the patient may have about the medication. If the pharmacist determines that a patient is an ideal candidate for the medication and the patient agrees, empagliflozin will be prescribed to the patient.

**Fig. 1 Fig1:**
[figure not shown]
Care processes and analysis of study arms. ^*^Analyses will include all patients identified in the VA dashboard

Approximately 30 days after starting the medication, a member of the study team calls the patient to assess for medication side effects. If the patient tolerates the medication, follow-up labs will be scheduled to reassess the patient’s basic metabolic panel. However, if the patient has side effects or concerns, the patient will receive a follow-up phone call and assessment by the pharmacist to determine if empagliflozin should be continued. If the one-month lab results come back abnormal, the patient will have a follow-up outreach to determine the appropriate course of action and to engage with the patient’s primary care team. If the lab results are stable and within normal limits, the patient will receive a letter with their lab results and continued care from their primary care team. Patients in the control arm will receive usual care while the first iteration of this program is ongoing and may be prescribed an SGLT2i, if recommended by their care team.

### Clinical team

There are two full-time equivalent (FTE) clinical pharmacists to carry out the intervention. In addition, to support patient outreach and follow-up, the team also includes one FTE for a medical assistant and one FTE for a licensed practical nurse (LPN).

### Outcomes

Our primary outcome is initiation of an SGLT2i among patients deemed candidates for SGLT2i as determined by the VA dashboard. Patients who filled an SGLT2i at any point during the study timeframe, as determined by electronic health record data, will be considered to have initiated the medication.

Secondary outcomes will include adherence to the medication 12 months after initial prescribing (defined by refills of their SGLT2i), as well as various process and safety measures, such as the number and percent of patients who obtained metabolic labs after SGLT2i initiation, abnormal lab results, including acute kidney injury, and defined reasons for declining or stopping the medication (including low blood pressure/hypotension and hypoglycemia). Secondary outcomes will also include the proportion of patients who decline the intervention and later obtain an SGLT2i from another source (which will be reported as a descriptive statistic only as Veterans in the usual care, unlike those in the intervention arm, cannot crossover to the alternative arm). In addition, we will examine the progression of kidney disease, defined as a 40% reduction in eGFR sustained for at least two measures. We will also measure the number of times eGFR is assessed as this may affect outcome ascertainment.

Exploratory outcomes will include rates of all-cause hospitalizations, initiation of dialysis, and major adverse cardiac events (nonfatal myocardial infarction, nonfatal stroke, and hospitalization for heart failure).

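### The primary outcome window runs past the point at which controls start outreach, so as written it counts second-wave control fills as usual-care initiation and pulls the difference toward zero

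*Protocol article*

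**What the plan says.** Four statements in the protocol article's Methods and Aims bear on the window.

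- **Outcomes.** The primary outcome is initiation of an SGLT2i among dashboard candidates. The operational rule counts as initiators "Patients who filled an SGLT2i at any point during the study timeframe", with fills taken from the electronic record. No end date is attached.
- **Study design and setting.** The only study period in the article begins in February 2022, and the study "will continue until all eligible Veterans in the region are offered the intervention, which is anticipated to be in 2025".
- **Patient selection and randomization.** "The controls will receive usual care until all eligible Veterans in the odd-numbered group have received the intervention". The next sentence reads: "At that time, even-numbered Veterans will also begin to receive the intervention".
- **Aims.** The hypothesis compares patients reached in the first iteration with "those receiving usual care while they await a future wave of this same interventional program".

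The Analysis section compares the two proportions with a two-sample test and gives no cut date or censoring rule. The note to Fig. 1 says that all patients identified in the dashboard are analysed.

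**The concern.** The hypothesis needs a control group that is still waiting. The outcome rule instead follows controls for as long as the study lasts, and the study lasts until they too have been offered the pharmacist programme. A control who fills an SGLT2i because of second-wave outreach is scored the same as one who started it under usual care.

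Applied to the end of that period, the primary comparison is immediate against delayed outreach. If outreach works, the second wave raises the control proportion and the reported difference understates the effect of the first wave. The error can only hide benefit, and a larger sample does not remove it. With no cut-off in the definition, the choice of data-cut date also drives the result and could be made after fills have been seen.

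**Working it through.** **Step 1: what the text implies about timing.** The controls' usual-care period ends when the odd-numbered group is complete (Patient selection and randomization). The study ends when all eligible Veterans in the region have been offered the intervention (Study design and setting). The second event includes controls and the first does not, so the second comes later. The interval between them is the second wave. It lies inside the study period, and so inside a window that accepts a fill at any time in that period.

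**Step 2: inputs.** The article states no initiation rates, effect size, sample size or power, so there is no figure to reproduce. The following are assumptions:

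- pc, pt: proportions initiated in control and intervention arms when the first wave ends.
- h = (pt − pc)/(1 − pc): extra uptake due to outreach.
- f: share of not-yet-initiated controls reached by the second wave before the data cut.
- Second-wave uptake equals h, with no other new starts in either arm.
- Two-sided 0.05 (the article gives 0.05 without sidedness) and 1:1 allocation (inferred from odd/even assignment).

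**Step 3: formula.** Control proportion at the data cut = pc + (1 − pc) × f × h = pc + f(pt − pc). The measured difference is therefore pt − pc − f(pt − pc) = (1 − f)(pt − pc).

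**Step 4: numbers.** Take pc = 10% and pt = 25%, so h = 0.15/0.90 = 0.167. At f = 0.5 the control proportion is 0.10 + 0.90 × 0.5 × 0.167 = 0.175, and the difference is 0.25 − 0.175 = 0.075. An illustrative 133 per arm gives 90% power for the undiluted difference.

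| f | Control | Difference (points) | Retained | Power, 133 per arm | Power, 500 per arm |
|---|---|---|---|---|---|
| 0 | 10.0% | 15.0 | 100% | 90% | >99% |
| 0.25 | 13.75% | 11.25 | 75% | 64% | 99.5% |
| 0.5 | 17.5% | 7.5 | 50% | 32% | 83% |
| 0.75 | 21.25% | 3.75 | 25% | 11% | 29% |
| 1 | 25.0% | 0 | 0% | 2.5% | 2.5% |

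The 2.5% in the last row is the chance of a significant result favouring the intervention when the expected difference is zero.

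**Step 5: sensitivity.**

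- *Other rates.* The retained share does not depend on the rates. For 30% v 15%, 15 points become 11.25, 7.5, 3.75 and 0 at f = 0.25, 0.5, 0.75 and 1. For 40% v 20%, 20 points become 15, 10, 5 and 0.
- *Background starts.* If a proportion b of the remaining patients in each arm also start during the extra time, the difference is (1 − b)(1 − f)(pt − pc). With b = 10% the retained shares are 90%, about 68%, 45%, 22–23% and 0. The longer window costs something even at f = 0.
- *Lower second-wave uptake.* If second-wave uptake is r × h, the retained share is 1 − f × r. With r = 0.5 and f = 1, half the difference survives: 15 × 0.5 = 7.5 points.

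**The case against.** The strongest reply is that the authors plainly mean a first-wave comparison. The abstract, Aims, Patient selection and randomization and Intervention sections all describe controls as waiting. Outcomes never defines its study timeframe, and the sentence on study duration describes how long the programme runs. Data-cut dates usually belong in a statistical analysis plan, which is not shown. The point about intent stands. It does not remove the finding, because the article does not leave the window open: it accepts a fill at any time, and only one study period is given. A later plan with a first-wave cut-off would be correcting that definition.

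Three stronger readings are tempting, and the document does not support them.

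- *The crossover remark is an outright contradiction.* Outcomes explains that one measure is descriptive only, "as Veterans in the usual care, unlike those in the intervention arm, cannot crossover to the alternative arm". A reader might set this against the planned second wave. During the first wave the remark is true, and it is evidence that a first-wave comparison is meant.
- *Fills before listing corrupt the outcome.* A reader might infer that an SGLT2i filled and stopped after February 2022 but before the list was pulled counts as initiation. That strains the word initiation. Such fills also precede the list date, which is the randomization date, so they should be about equal in odd and even SSNs. Starting the window at the index date settles it.
- *Every clinical outcome is contaminated.* The study timeframe is attached only to the primary outcome. Adherence has its own 12-month window, and several process measures concern only initiators or decliners. For the remaining clinical outcomes the article states no window, so contamination is possible but not shown.

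**Conclusion.** The point holds for the primary outcome. Taken together, the outcome rule, the stated study period and the planned start of outreach to controls put second-wave control fills into the control proportion, which conflicts with the hypothesis in Aims. The bias is toward zero whenever the second wave produces additional fills.

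Its size is not fixed by the document. Under equal uptake and no other new starts the retained share is 1 − f. A reader might infer that the trial must show no difference, because the stated end of the study corresponds to offering outreach to all controls. That follows only if all controls are reached, uptake equals the first wave's, late-contacted controls have time to fill, and the data are cut at programme end. None of these is established, and the text does not show that the analysis will be run this way. What is established is that the written definition does not match the comparison it is meant to serve.

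**What to change.** Redefine the primary outcome as the first SGLT2i fill from the patient's index (list) date up to the date on which second-wave outreach to even-SSN Veterans opens. Apply the same calendar cut-off to both arms. As Patient selection and randomization now reads, this is one network-wide date, because the second wave depends on completing the whole odd-numbered group. If it will in fact open site by site, use the site's date for odd and even patients alike. Include only patients listed before the cut-off.

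Use the same cut-off for other between-arm comparisons that have no window of their own, and censor both arms at that date in the Kaplan-Meier and Cox analyses. The crossover sentence then needs only the qualifier that it applies before the second wave.

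The change is to wording and analysis. Index dates come from the list extractions and fills from the electronic health record. The article does not say that the second-wave opening date is recorded, so the sponsor should document it and fix the rule before outcome data are examined. The cost is that some late follow-up leaves the comparison.

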### Analysis

We will assess balance in baseline clinical and demographic characteristics between the two study arms with chi-square tests for categorical variables (e.g., patient sex) and Kruskal-Wallis test assuming unequal variances for continuous variables (e.g., patient age, baseline eGFR as calculated by the final serum creatinine concentration before the index date via the most recent CKD-EPI equation) [28]. The primary and secondary outcomes, the proportion of initiation of SGLT2i or proportion with a safety or process measure, respectively, will be compared between the study arms via the Two-Sample Proportions test. For binary exploratory outcomes, such as initiation of dialysis, major adverse cardiac events, and progression of kidney disease, we will also compare proportions between the arms via Two-Sample Proportions test. When these binary outcomes have an associated time of occurrence, Kaplan-Meier analysis will be used to assess the cumulative incidence of these events. We will use logistic regression and Cox proportional hazards models for adjusted analyses accounting for patient medical and demographic characteristics for binary and time-till-event outcomes. A Type-I-Error rate of 0.05 will be used for the primary outcome to declare significance and we will report the associated 95% confidence interval. Secondary outcomes will also use a p-value of < 0.05 and 95% confidence intervals.

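### Twelve-month adherence and post-initiation labs exist only in patients who start an SGLT2i, yet the plan tests secondary outcomes between arms, and that comparison is not protected by the SSN allocation

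*Protocol article*

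**What the plan says.** The Outcomes section of the protocol article names as secondary outcomes "adherence to the medication 12 months after initial prescribing (defined by refills of their SGLT2i") and "the number and percent of patients who obtained metabolic labs after SGLT2i initiation". Both are timed from the start of treatment. The same list includes "defined reasons for declining or stopping the medication", where stopping also presupposes a start.

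The Analysis section takes the primary and secondary outcomes together. It says that the initiation proportion, or the "proportion with a safety or process measure, respectively, will be compared between the study arms via the Two-Sample Proportions test". It adds: "Secondary outcomes will also use a p-value of < 0.05 and 95% confidence intervals". No denominator is given for the measures timed from initiation.

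One secondary outcome is exempted from testing. The proportion who decline and later obtain the drug elsewhere is the one "which will be reported as a descriptive statistic only as Veterans in the usual care" cannot cross over. The footnote to Fig. 1 is the only general statement on the analysis population: "Analyses will include all patients identified in the VA dashboard".

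**The concern.** The odd/even SSN rule makes the arms comparable over everyone on the dashboard list. It does not make starters in one arm comparable with starters in the other. Under Intervention, a patient in the active arm can start after outreach, a pharmacist's judgement and the patient's own agreement. A control patient starts only if the usual care team recommends it. The Aims hypothesise that more patients will start in the intervention arm. If the programme succeeds, its starters will therefore include people with no counterpart among the control starters.

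A test confined to starters could then reach p < 0.05 even if the programme changed nobody's adherence, and the result would be read as an effect of the programme. Persistence bears on whether the strategy is worth scaling up, which the Discussion raises, so a false signal in either direction would matter.

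**Working it through.** The plan states no sample size, power or event rate, so there is no figure to reproduce. The structural point comes from reading Outcomes, Analysis and the Fig. 1 footnote together. The arithmetic below only illustrates the size, and every rate and sample size in it is an assumption.

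**Model.** Let *a* be the share who start under either arm and *c* the extra share who start only because of outreach. Let *h_a* and *h_c* be 12-month adherence in these two groups, the same in both arms, so the true effect on adherence is zero. The model assumes that outreach never prevents a start.

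**Starters only.**
- Control: *h_a*
- Intervention: (*a h_a* + *c h_c*)/(*a* + *c*)
- False difference: [*c*/(*a* + *c*)] × (*h_c* − *h_a*)

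**All patients, started and adherent.**
- Control: *a h_a*
- Intervention: *a h_a* + *c h_c*

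With *a* = 0.10 and *c* = 0.20:

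| *h_a* / *h_c* | Starters: control | Starters: intervention | False difference | All patients: control vs intervention |
|---|---|---|---|---|
| 0.80 / 0.60 | 80.0% | (0.08 + 0.12)/0.30 = 66.7% | -13.3 points | 8.0% vs 20.0% |
| 0.60 / 0.80 | 60.0% | (0.06 + 0.16)/0.30 = 73.3% | +13.3 points | 6.0% vs 22.0% |
| 0.75 / 0.75 | 75.0% | (0.075 + 0.15)/0.30 = 75.0% | 0 | 7.5% vs 22.5% |

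**Probability that the starters-only test rejects** (two-sided 0.05, normal approximation). With *N* per arm the test compares *Na* control starters with *N*(*a* + *c*) intervention starters, for example 50 with 150 at *N* = 500.

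| Scenario | *N* = 500 | *N* = 1000 | *N* = 2000 |
|---|---|---|---|
| *a* = 0.10, *c* = 0.20, 0.80/0.60 | 0.42 | 0.73 | 0.96 |
| *a* = 0.10, *c* = 0.20, 0.60/0.80 | 0.43 | 0.70 | 0.94 |
| *a* = *c* = 0.10, 0.80/0.70 (difference -5.0 points) | 0.09 | 0.15 | 0.27 |
| equal adherence | 0.05 | 0.05 | 0.05 |

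The nominal rate is exceeded whenever outreach-induced starters differ in adherence from usual-care starters. The all-patients comparison keeps the allocation. In this model, however, its difference is *c h_c* and arises wholly from extra starts, so it does not isolate persistence.

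**The case against.** The strongest reply is that the plan nowhere restricts these tests to starters, and that the Fig. 1 footnote points to everyone on the dashboard. A reader might infer from the outcome definitions that a starters-only denominator is fixed. The text does not go that far. But the footnote does not settle the matter either, because it does not say how a patient with no first prescription scores on a measure timed from that prescription. If such patients count as failures, the outcome is no longer adherence but initiation plus adherence, and should be named so. If they are dropped, the selection problem stands.

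A second reply is that denominators belong in an SAP that is not shown. That would hold for a bare omission. Here the article fixes both the outcome and the between-arm test, and exempts only one other outcome from testing.

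Third, the Analysis section describes the tested secondary outcomes as safety or process measures, while Outcomes lists adherence beside those. This is a real ambiguity for adherence, but the sentence opens with all primary and secondary outcomes. Lab completion is a process measure on any reading.

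Fourth, the planned adjusted models may reduce measured imbalance among starters, but they cannot restore the allocation.

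Two stronger readings are tempting and unsupported. One is that abnormal labs and acute kidney injury share the defect. Outcomes ties only the obtaining of labs to initiation, and the other two can be counted in every allocated patient. The other is that the bias will make the programme look harmful. Neither its direction nor its size can be derived from the document.

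**Conclusion.** The point holds for 12-month refill adherence and for lab completion after initiation. As written, they are sent to a between-arm test although they are defined only after an event that the intervention is meant to change. Under the assumed rates the false difference runs from none to about 13 points in either direction, with rejection probabilities from the nominal 0.05 up to 0.96. These figures rest on invented start and adherence rates and on the assumption that outreach prevents no starts.

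The primary outcome is unaffected, as are outcomes that exist in every patient, such as eGFR decline and hospitalisation. The change is worth making because a significant secondary result on these measures could not be attributed to the programme.

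**What to change.** 1. Make the between-arm test the proportion of all dashboard-identified patients with SGLT2i supply at 12 months from the index date, non-starters counting as no, assessed before controls are offered the intervention. Call it a measure of initiation plus persistence.
2. Report refill adherence and post-initiation lab completion among starters by arm, with denominators, labelled as a non-randomised description and without a between-arm p-value.
3. Keep abnormal labs and acute kidney injury as between-arm comparisons in all allocated patients.

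The cost is a change of wording, and the refill data are the same. The plan gives up a formal test of persistence among starters. The new outcome overlaps with the primary outcome. Because outreach follows the list date and is rolled out over time, patients reached late will have had less than 12 months on the drug when assessed, which the report should state.
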